**Fig 1 pone.0312970.g001:**
[figure not shown]
Illustration of the difference pathways which may be reflected by protein associations with genetic variables and disease liability. Panel A shows the relationship between genetic variants (G1-9), upstream proteins (P1-6) and downstream proteins (P7-9) via the disease liability pathways. Panel B shows the relationship between SNPs and upstream protein P6. Panel C shows the relationship between SNPs and downstream protein P9.

### Aims and objective

Cancer early detection remains a challenge, with a lack of specific biomarkers for lung and colorectal cancer. This research aims to identify protein level changes that are causally downstream of genetic liability to lung cancer and colorectal cancer for use as potential biomarkers for these cancers. To achieve this, we will use a combination of PRS, observational analyses, bidirectional Mendelian Randomization and colocalization approaches.

## Methods and analysis

### Polygenic risk score analyses

PRS can be developed using GWAS summary statistics on the associations of many SNPs across the genome with cancer. In this way millions of SNPs can be combined to develop an individual’s PRS for a cancer. A PRS is the sum of the number of copies of risk alleles individuals have for SNPs across the genome, weighted by the effect size of these SNPs in relation to the disease of interest, in this case, cancer [19]. While the initiation of cancer and the factors that contribute to the onset and progression of cancer are still not fully understood [20]; by calculating a PRS using data from all SNPs across the genome, SNPs involved in initiation, promotion and progression of cancer will be captured by this score, reflecting the complex process of cancer development [18].

In this study, PRS will be calculated for UKB participants (Application ID: 15825/81499) with proteomic measurements (N = 49,542), individuals with sex-mismatch (derived by comparing genetic sex and reported sex) or individuals with sex-chromosome aneuploidy will be excluded from the analysis (N = 814) as well as highly related individuals related to a 3^rd^ degree to >200 individuals (N = 2) [21]. For colorectal cancer, we will use effect weights derived from GWAS summary statistics of the: i) Genetics and Epidemiology of Colorectal Cancer Consortium (GECCO) (GWAS Catalog Accession: GCST90255675) for Europeans; and ii) the Asia Colorectal Cancer Consortium (ACCC)/Korean-National Cancer Centre CRC Study 2 (Korea-NCC2) for GWAS summary statistics for East Asians. For lung cancer, we will use effect weights derived from GWAS summary statistics from the International Lung Cancer Consortium (ILCCO) (GWAS Catalog Accession: GCST004748). Sample selection and quality control within these studies has been previously described [22,23].

PRS will be derived from the PRS-CS approach, using summary statistics from GWAS for the cancer of interest along with an external linkage disequilibrium (LD) reference panel corresponding to the ancestry of the GWAS. The continuous shrinkage approach incorporates the strengths of the GWAS associations into the shrinkage applied to shrink small SNP effects towards zero, while large effects are unaffected [24], generating a posterior effect size for each SNP [25]. These weights will be used to calculate the PRS of UK Biobank participants for colorectal and lung cancer, calculating the sum of risk increasing alleles across all genetic variants weighted by the effect sizes generated by PRS-CS [25,26]. PRS-CSx applies the same methodology as PRS-CS to multi-ancestry GWAS summary statistics, improving generalisability of results to more ancestry groups within the global majority by allowing the use of different ancestry GWAS summary statistics and LD panels for those populations [27]. In an effort to reduce the Eurocentric bias and to increase power in addition to developing a European PRS, we will be utilising GWAS summary statistics for colorectal cancer from European and East Asian ancestries to develop polygenic risk scores [22,28,29].

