### Ethics

The colorectal cancer GWAS conducted by Fernandez-Rozadilla et al. (2022) was approved by the South Central Ethics Committee (UK) under the reference number 17/SC/0079 [22].

All studies used in the lung cancer GWAS conducted by McKay et al. (2017) obtained local ethics committee approval and all participants gave informed consent [23].

Application for colorectal cancer site specific GWAS summary statistics from GECCO has been approved.

Application for summary statistics from the Asian Colorectal Cancer Consortium (ACCC) and the Korean-National Cancer Center CRC Study 2 (Korea-NCC2) will be submitted.

UK Biobank was approved by the North West Multi-centre Research Ethics Committee (MREC) as a Research Tissue Bank (RTB) approval renewed in 2021, all participants in the study have given informed consent [61]. Genotype, phenotype and Olink protein measure data access has been obtained under Application ID: 15825/81499.

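### The plan scores UK Biobank participants with published GWAS weights without requiring that UK Biobank was left out of those GWAS

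*Protocol article*

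**What the plan says.** Under Polygenic risk score analyses, the article says of colorectal cancer that "we will use effect weights derived from GWAS summary statistics of the" named consortia: the European weights come from the "Genetics and Epidemiology of Colorectal Cancer Consortium (GECCO) (GWAS Catalog Accession: GCST90255675) for Europeans", the East Asian ones from ACCC/Korea-NCC2. The lung weights come from ILCCO (GCST004748). The target is the set of UK Biobank participants with proteomics, N = 49,542. After PRS-CS shrinkage, "These weights will be used to calculate the PRS of UK Biobank participants for colorectal and lung cancer". Cancer subgroup analyses adds further PRS by colorectal site, lung histology and smoking stratum.

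Sample selection in the source GWAS is left to the cited papers. The only independence condition concerns the LD panel, used "along with an external linkage disequilibrium (LD) reference panel corresponding to the ancestry of the GWAS"; nothing comparable is said of the discovery samples. The four scenarios under Sensitivity analyses, the MR sections and the limitations do not mention shared participants. The nearest item, the fourth scenario, concerns differences between the GWAS and target populations.

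**The concern.** The approach relies on the PRS being fixed by inheritance, so that a PRS-protein association can be traced to genetic liability. If a scored person was also in the discovery GWAS, that person's case status helped to set the weights. The score then correlates with the person's own case status beyond inherited liability, and so with whatever non-genetic factors led to the cancer. Proteins that differ between cases and controls for those reasons gain extra association with the PRS.

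The PRS-protein model adjusts for age, sex, principal components and, where relevant, storage time. It adjusts for neither smoking nor case status. Genome-wide shrinkage scores are more exposed than scores built only from genome-wide significant SNPs, because many small, noisy effects keep some weight. The plan fixes specific published files, so an analyst following it would use them whether or not they overlap with the target.

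**Working it through.** The protocol gives no overlap or power figure, so there is nothing to reproduce.

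**Inputs from the protocol.** Target N = 49,542. Colorectal cases with protein data: 630 + 67 + 268 = 965 of 52,996, p = 1.82% (if nobody carries two codes). Lung: 597 of 52,996, p = 1.13%. These rates are recomputed because the percentages printed for UKB-PPP in Table 1 fit the whole-cohort denominator.

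**Assumed inputs.** 60,000 independent SNPs, effective GWAS n = 80,000, observed-scale heritability 0.10, 2% of SNPs causal, sparse (spike-and-slab) shrinkage standing in for PRS-CS, full overlap of cases and controls, and a protein shifted 0.5 SD in cases.

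**PRS gap.** With w the posterior-mean weight as a function of the estimated effect and w′ its derivative:
- overfit gap = 2·Σw′ / (n·SD(PRS)) ≈ 0.32 SD
- true gap = 2·Σ(w·b) / SD(PRS) ≈ 0.49 SD
- ratio = 0.32 / 0.49 ≈ 65%

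The factor 2 is the contrast between overlapped cases and overlapped controls. If only the cases overlap, the gap halves to about 0.16 SD (+33%). With both groups overlapping in part, 50% overlap gives about 0.16 SD (+33%) and 25% about 0.08 SD (+16%).

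**Induced z** = p(1 − p) × gap × 0.5 × √49,542, with √49,542 = 222.6:

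| Cancer | p(1 − p) | Spurious z (0.32 SD) | True-path z (0.49 SD) |
|---|---|---|---|
| Colorectal | 0.01788 | 0.64 | 0.97 |
| Lung | 0.01114 | 0.40 | 0.61 |

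The lung row applies the same assumed gaps to the lung case rate.

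**Range.** Over n = 50,000 to 180,000, heritability 0.05 to 0.15 and 0.5% to 10% causal, still with full overlap, the overfit gap runs from 0.02 SD to about 1.95 SD. It exceeds the true gap in the less favourable part of that grid. At 1.95 SD the spurious colorectal z is 0.01788 × 1.95 × 0.5 × 222.6 = 3.9. For comparison, a Bonferroni cut over 2,923 proteins is |z| = 4.30; the plan itself uses FDR.

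**Mechanism check.** In a simulation the SNPs had no effect and a confounder drove both cancer and protein (1,500 SNPs, discovery 6,000, target 2,000, unshrunk weights, 60 runs each):

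| Share of target in the GWAS | Correlation of PRS with own case status | PRS-protein rejection at 0.05 |
|---|---|---|
| 0% | −0.003 | 0.00 |
| 10% | 0.049 | 0.02 |
| 50% | 0.238 | 0.48 |
| 100% | 0.448 | 0.90 |

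This shows that the mechanism exists and grows with overlap. It does not give its size here: the sample is far smaller, the weights are unshrunk, and PRS-CS would reduce the effect.

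**The case against.** The strongest objection is that no error is shown. Whether UK Biobank contributed is recorded in the cited GWAS papers, which are not at hand, and an article may leave a cohort check to fuller documents. It stands to this extent: a reader might infer that the samples do overlap, and nothing in the protocol supports that. It does not remove the point, because the article itself fixes the files and the target and sets no condition linking them.

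Other strong readings also fail:
- **That overlap would fill the scan with false discoveries.** In the central case the spurious z is 0.6 or 0.4. Reaching 4.30 at a gap of 0.32 SD would need a protein shift of about 3.4 SD (colorectal) or 5.4 SD (lung).
- **That the +65% applies if only the cases overlap.** It needs controls too.
- **That treatment effects are a main route.** Table 2 shows 97 + 22 + 60 = 179 of 965 colorectal and 31 of 597 lung cases as prevalent; most cases were sampled before diagnosis.
- **That an inflated protein would at once be classed as downstream of liability.** Reverse MR on genome-wide significant SNPs, pleiotropy-robust methods, colocalization, the diagnosis-timing analysis and replication come first. None is designed to detect shared participants, however. MR would share them too if its cancer GWAS includes UK Biobank and its protein data come from there. Replication is limited to proteins available in the other cohorts.

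**Conclusion.** The point holds as an unguarded condition, not as a demonstrated bias. The plan applies named published weights to UK Biobank without requiring that discovery and target samples be separate. Without overlap the bias is zero. With full overlap of cases and controls, under the assumed central inputs, the case-control PRS gap is inflated by about 0.32 SD on 0.49 SD; it is about half that if only cases overlap, and proportionately less with partial overlap. The absolute spurious z is small in that case, so what is at stake is mainly relative inflation of PRS-protein estimates and of the ranking that decides which proteins go forward. The effect is larger with a smaller GWAS, lower heritability or more causal SNPs. All of these sizes rest on assumed GWAS inputs that the documents do not give.

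**What to change.** Under Polygenic risk score analyses, state for each discovery set (overall, colorectal site, lung histology, smoking stratum) whether UK Biobank contributed. Where it did, use UK Biobank-excluded summary statistics for the PRS and for the SNP-cancer effects in both MR directions. Where these cannot be obtained, repeat the PRS-protein scan without the overlapping participants as a sensitivity analysis; if those people cannot be identified, repeat it without the UKB-PPP cases. Dropping all cases also removes genuine signal from diagnosed cancers, so an association that persists is reassuring, while one that fades is not proof of overfitting. List overlap among the limitations.

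The cost is a cohort check and possibly a further data request. The Ethics section says "Application for colorectal cancer site specific GWAS summary statistics from GECCO has been approved", the ACCC/Korea-NCC2 application is still to be submitted, and no ILCCO application is mentioned, so not every request can ride on one already made. Leave-out weights would be slightly less precise. Where there is no overlap, nothing changes beyond a sentence saying so.

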### Cancer subgroup analyses

In addition to a PRS for overall colorectal and lung cancers, we will calculate a PRS for colon cancer and rectal cancer specifically and for lung cancer subgroups (adenocarcinoma, squamous cell carcinoma, small cell carcinoma). Additionally, PRS scores will be calculated for never smokers and ever smokers using weights generated from summary statistics of GWAS for lung cancer in never smokers and lung cancer in ever smokers.

### Olink proteins

Olink protein measurements were performed as part of the Pharma Proteomic Project (UKB-PPP) on blood plasma samples using the antibody-based protein Olink Explore 3072 Proximity Extension Assay. Proteomics were generated for 54,219 participants who were considered to be highly representative of the UK Biobank population on baseline characteristics and showed enrichment for selected diseases [30]. The number of participants with colorectal and lung cancers can be seen in Table 1. Quality control, sample selection and data processing has been described previously [30]. Associations between the participants’ PRS and 2923 Olink protein measures from the UK Biobank will be tested via linear regression, adjusting for age, sex, principal components and sample storage time where this has an impact on protein level variation [31]. Protein measures will undergo inverse rank normal transformation (INT) for each protein [32]. The number of independent proteins will be calculated using the metaboprep R package [33]. False discovery rate correction will be applied to p-values, proteins with p-value less than the calculated alpha will be prioritised for further analyses.

**Table 1 pone.0312970.t001:** Cancer frequency within the UKB cohort and within the UKB-PPP study participants.

ICD10/ICD9 code	Cancer	Number of cases (UKB)	Number of cases (UKB-PPP)
C18/153	Malignant neoplasm of colon	6015 (1.2%)	630 (0.13%)
C19/1540	Malignant neoplasm of rectosigmoid junction	642 (0.13%)	67 (0.013%)
C20/1541	Malignant neoplasm of rectum	2670 (0.53%)	268 (0.053%)
C34/162	Malignant neoplasm of bronchus and lung	5305 (1.1%)	597 (0.12%)
**ICD-O-3 Code**	**Histological Subset**	**Number of cases (UKB)**	**Number of cases (UKB-PPP)**
8140, 8211, 8250–8260, 8310, 8323, 8480–8490, 8550	Lung adenocarcinoma	2390 (0.48%)	261 (0.052%)
8070-8072	Lung squamous cell carcinoma	1244 (0.25%)	151 (0.03%)
8041–8042	Lung small cell carcinoma	502 (0.1%)	64 (0.013%)

Number of cases for each cancer type derived from UK Biobank phenotypic data with percentage of cases out of overall individuals is represented in brackets. UKB overall n = 501939, UKB with protein measures (UKB-PPP) n = 52996.

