### Study design

MR will be performed in the forward and reverse direction: forward MR, where the protein is the exposure and cancer is the outcome, will be used to estimate the effect of selected proteins on the cancer of interest and reverse MR, where cancer is the exposure and protein levels are the outcomes, will be used to estimate the effect of cancer liability on circulating protein concentration [17]. Forward MR will be performed using cis-pQTLs to instrument proteins identified as being associated with the cancer PRS, the threshold for these will be p < 3.4 x 10^−11^ [40]. Cis-pQTLs will be defined as within < 1Mbp of the protein coding gene and trans-pQTLs will be defined as > 1Mbp away from the protein coding gene [41]. Reverse MR will be performed using SNPs associated with the cancer PRS at a threshold of p < 5 x 10^−8^ excluding cis-pQTLs for the protein. If association is found in the forward direction this may suggest that the protein is causal for the cancer but if association is found in the reverse direction this may suggest that genetic liability to cancer is causing the protein level change [17]; to elucidate this causality, different MR estimation methods will be employed, the application and conditions of these are described below.

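### The discovery score keeps each protein's own cis region, so one strong shared locus can produce a hit, and the polygenic association is never re-tested without that region

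*Protocol article*

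**What the plan says.** Under Polygenic risk score analyses, the score is built "calculating the sum of risk increasing alleles across all genetic variants weighted by the effect sizes generated by PRS-CS", and the section justifies this "by calculating a PRS using data from all SNPs across the genome". It adds that continuous shrinkage pulls small effects towards zero "while large effects are unaffected", so a strong cancer locus keeps its weight.

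Under Olink proteins, "2923 Olink protein measures from the UK Biobank will be tested via linear regression". The covariates named there are sex, age, principal components and, if it affects the protein, storage time. No cis region is left out and no cis-pQTL is a covariate. For multiplicity, "False discovery rate correction will be applied to p-values"; the level is not given.

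Cis variants first appear under Study design, for proteins already selected. There they serve as instruments in forward MR, while reverse MR uses SNPs at p < 5 × 10⁻⁸, "excluding cis-pQTLs for the protein". Cis is defined as within 1 Mbp of the coding gene. The Fig 3 caption confirms the order: proteins first, cis-pQTLs second.

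**The concern.** The aim is to find proteins causally downstream of genetic liability. The Introduction argues that a PRS suits this aim because, for a downstream protein, every variant in the score could contribute, whereas most are unrelated to a protein that causes cancer. That argument weakens if one locus can carry the whole association. A variant near the protein's gene may be in the score because the locus affects cancer, and may also shift the protein directly. The regression then detects that locus even when liability has no effect on the protein.

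The discovery regression returns one coefficient for the whole score and does not show whether the signal is spread over the genome or sits in one place. At stake is how a discovery hit is interpreted, and whether any later step can tell a single-locus hit from a polygenic one.

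**Working it through.** The plan gives no power or alpha figure for this scan, so there is nothing to reproduce.

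**Inputs from the Protocol article.** N = 49,542 participants with proteomic measurements. If the exclusions of 814 and 2 are still to be taken off, N = 49,542 − 816 = 48,726. There are 2923 proteins.

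**Assumed inputs (not in the document).**
- a: share of PRS variance carried by the cis region.
- b: share of protein variance explained by the cis-pQTL.
- r²: squared correlation between the regional part of the score and the cis-pQTL.
- Reference threshold: 0.05/2923 = 1.71 × 10⁻⁵ two-sided, z = 4.30. This is Bonferroni, used as a strict yardstick.

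**Step 1: signal from one locus with no liability effect.** The correlation of PRS and protein is √(a·b·r²), so z ≈ √(N·a·b·r²). For example, √(49,542 × 0.005 × 0.10) = √24.8 = 5.0. At N = 49,542:

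| a | b | z, r² = 1 | z, r² = 0.5 | z, r² = 0.1 |
|---|---|---|---|---|
| 0.5% | 10% | 5.0 | 3.5 | 1.6 |
| 1% | 5% | 5.0 | 3.5 | 1.6 |
| 0.3% | 30% | 6.7 | 4.7 | 2.1 |
| 0.1% | 10% | 2.2 | 1.6 | 0.7 |

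Using 48,726 instead lowers z by under 1%.

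**Step 2: how much weight the locus needs.** For 80% power at the reference threshold under complete LD, a·b = (4.30 + 0.84)²/48,726 = 5.4 × 10⁻⁴. The region must then carry 1.1% of PRS variance if b = 5%, 0.54% if b = 10%, 0.27% if b = 20%, 0.18% if b = 30% and 0.11% if b = 50%. A weak cis-pQTL with b = 1% would need 5.4%. With an FDR cut-off at an assumed 5% level and 50 discoveries (p < 0.05 × 50/2923 = 8.6 × 10⁻⁴, z = 3.33), these shares fall by about a third.

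**Step 3: an average locus.** Assuming a genome of about 3,000 Mb, a 2 Mb window carries on average 2/3,000 = 0.067% of the score. Under complete LD, z is √(49,542 × 0.00067 × 0.10) ≈ 1.8 for b = 10% and about 3.1 for b = 30%. Reaching 4.3 would need b of about 56%. Only regions well above average weight matter.

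**Step 4: simulation.** N = 48,726, zero liability effect, inverse-normal transformed protein, 300 runs per setting, p < 1.71 × 10⁻⁵. With the full score the hit rate was 84% (a = 0.2%, b = 30%), 100% (0.5%, 20%) and 100% (1%, 10%). With the cis variant removed it was 0% each time. The simulated score contains the causal variant itself, so this confirms the algebra under complete LD and is not separate evidence on size.

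**Step 5: what exclusion costs a polygenic signal.** If the protein responds to liability as a whole and the region is uncorrelated with the rest of the score, z is multiplied by √(1 − a). For a = 0.5% that is √0.995 = 0.997, and for a = 2% it is √0.98 = 0.990. A genuinely polygenic hit barely changes.

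**The case against.** The plan treats the PRS scan as a screen. Its Sensitivity analyses section says openly that a hit may reflect forward causation, reverse causation, horizontal pleiotropy or population stratification. Forward MR on cis-pQTLs, reverse MR without them, pleiotropy-robust estimators, clustering and colocalization then sort the hits. A PRS association alone is not called downstream of liability. All of this stands, as do the following limits on stronger readings.

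- A reader might infer that single-locus hits fill the discovery list. The document supports no count or fraction of affected proteins, and step 3 shows that an average region does not give a hit.
- A reader might infer that the FDR is broken. The null tested is no PRS-protein association, and a cis-driven association is a true rejection of it. Extra true rejections can loosen a step-up cut-off, but the size of that effect is not shown.
- A reader might infer that sub-threshold cis variants bias reverse MR. They are not instruments there, so they cannot.
- The Study design section does not say which threshold defines the cis-pQTLs removed from reverse MR, so the plan cannot be said to leave correlated cis variants in.

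What the objection does not answer is narrower. The Strengths section expects the genome-wide score to be more powerful than one built on genome-wide significant SNPs. A null reverse MR on those SNPs therefore cannot separate a cis-driven hit from a diffuse polygenic one. Colocalization asks whether a variant is shared at a locus; a shared cis variant passes, and the result says nothing about the rest of the score.

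**Conclusion.** The point holds as a gap in how discovery hits can be interpreted. It is not a contradiction in the plan or an unrecognised bias in the final classification. A protein can be selected through its own cis region alone when that region has above-average PRS weight and is in strong LD with a strong cis-pQTL: z is about 5.0 for 0.5% and 10% under complete LD, 3.5 at r² = 0.5, and 2.2 for 0.1% and 10% under complete LD. The shares, protein variances and LD values are assumptions, and 4.3 is a Bonferroni yardstick rather than the plan's cut-off. No planned step re-tests the polygenic association without the cis region.

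**What to change.** - Keep the full-score regression as the screen and as the entry to forward MR.
- For each protein that passes (or for all 2923), also regress the protein on the PRS without variants within 1 Mbp of its gene, using the plan's own cis definition. This is the full score minus the regional subtotal. Report both results.
- Require association with the cis-excluded score, at a level fixed in advance, as supporting evidence before describing a protein as downstream of liability. Label proteins whose signal vanishes as cis-driven.
- In reverse MR, state that the same 1 Mbp window is excluded.

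The cost is one more regression per protein and score. Forward-causal proteins acting in cis will lose signal in the cis-excluded run, which is why the full-score result is kept. Hits driven by a single trans-pQTL are not removed, so the planned pleiotropy analyses are still needed.
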